## Abstract

**Background:**

Delirium is associated with substantial morbidity and mortality rates in elderly hospitalised patients, and a growing problem due to increase in life expectancy. Implementation of standardised non-pharmacological delirium prevention strategies is challenging and adherence remains low. Pharmacological delirium prevention with haloperidol, currently the drug of choice for delirium, seems promising. However, the generalisability of randomised controlled trial results is questionable since studies have only been performed in selected postoperative hip-surgery and intensive care unit patient populations. We therefore present the design of the multicenter, randomised, double-blind, placebo-controlled clinical trial on early pharmacological intervention to prevent delirium: haloperidol prophylaxis in older emergency department patients (The HARPOON study).

**Methods/Design:**

In six Dutch hospitals, at-risk patients aged 70 years or older acutely admitted through the emergency department for general medicine and surgical specialties are randomised (n = 390) for treatment with prophylactic haloperidol 1 mg or placebo twice daily for a maximum of seven consecutive days. Primary outcome measure is the incidence of in-hospital delirium within seven days of start of the study intervention, diagnosed with the Confusion Assessment Method, and the Diagnostic and Statistical Manual of Mental Disorders, fourth edition criteria for delirium. Secondary outcome measures include delirium severity and duration assessed with the Delirium Rating Scale Revised 98; number of delirium-free days; adverse events; hospital length-of-stay; all-cause mortality; new institutionalisation; (Instrumental) Activities of Daily Living assessed with the Katz Index of ADL, and Lawton IADL scale; cognitive function assessed with the Six-item Cognitive Impairment Test, and the Dutch short form Informant Questionnaire on Cognitive Decline in the Elderly. Patients will be contacted by telephone three and six months post-discharge to collect data on cognitive- and physical function, home residency, all-cause hospital admissions, and all-cause mortality.

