#### Secondary outcome measures

Severity and duration of delirium; number of delirium-free days; hospital length-of-stay; adverse events; all-cause mortality in-hospital and within six months post-discharge; cognitive and physical function at baseline, three, and six months post-discharge; new institutionalisation post-discharge; number of hospital admissions within six months post-discharge.

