### Data collection

Data will be mainly collected by two observers, a physician ([name]) and geriatric nurse [name] trained according to the Good Clinical Practice (GCP) principles. Participants’ demographic data, medical history, (prescription) medication history on admission (including the use of sleep medication and antidepressants), presence of sleep-wake cycle disturbances, visual and/or hearing impairment, substance use, and vital parameters will be documented. Medical history and (prescription) medications will be coded according to the World Health Organization’s International Statistical Classification of Diseases and Related Health Problems 10^th^ revision (ICD-10)
[16], and the Anatomical Therapeutic Chemical (ATC) Classification System
[17]. Severity and number of co-morbidities are listed according to the Charlson comorbidity index using the ICD-10 coding algorithm
[18,19]. Physical function is assessed with the Katz Index of Independence in Activities of Daily Living (ADL)
[20,21] and the Lawton Instrumental Activities of Daily Living (IADL) scale
[22]. The Six Item Cognitive Impairment Test (6-CIT) is used to evaluate participants’ cognitive function
[23-25]. Primary caregivers are asked to complete the IQCODE-N in order to reflect on the participant’s cognitive function prior to hospitalisation
[26]. The Confusion Assessment Method (CAM) will be used to diagnose delirium according to the Diagnostic and Statistical Manual of Mental Disorders, Fourth edition (DSM-IV) delirium criteria during the study intervention period, and to ensure delirium is not present on study inclusion
[27]. Nurses register the Delirium Observation Screening (DOS) scale three times a day (once every day, evening and night shift) during the intervention period to evaluate delirium symptoms
[28,29]. Once delirium is established, one of the observers will perform the DRS-R-98 once-daily to assess delirium severity and duration

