### Follow-up assessments

Three and six months after discharge, patients are contacted by telephone by one of the observers to perform the Katz ADL, the Lawton IADL scale, and the 6-CIT, and to obtain data on home residency, hospital admissions, (recurrent) delirium, and all-cause mortality.

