### Sample size calculation

The primary study objective is to evaluate the effect of prophylactic haloperidol compared to placebo for the incidence of in-hospital delirium within seven days of start of the study intervention. Based on previous studies, we expect the incidence of delirium in our target patient population currently to be 20%. Aiming for an absolute reduction of 10% in the haloperidol intervention group, with the significance level set at 5%, inclusion of n = 195 patients per study arm (390 patients in total) will give us a power of 80% to detect differences with a two-sided alpha of 0.05.

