[23]. Although the 6-CIT has not been validated for telephone administration, we considered it to be accurate for use over the telephone given that it includes diagnostic properties (e.g. temporal orientation, and object recall) similar to a six-item screener suitable for telephone administration
[39]. The Katz ADL has been shown a reliable way to collect data on ADL by telephone
[40]. Telephone follow-up was chosen because it is safe and more efficient than re-inviting subjects for a face-to-face interview.

In conclusion, the HARPOON study is a well-designed double-blind, placebo-controlled RCT that we believe will provide relevant information on the efficacy and safety of early administration of low-dose haloperidol for preventing delirium in at-risk elderly patients in the hospital setting, and its effects on post discharge outcomes. The predicted study completion is May 1^st^ 2015.

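### The IQCODE-N is named as an instrument for the secondary cognitive outcome, but it is scheduled only as a rating of function before admission, so the 6-CIT is the only cognitive measure that can show a treatment effect

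*Protocol article*

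**What the plan says.** The protocol article deals with cognition in five places.

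- The abstract (Methods/Design) lists as a secondary outcome "cognitive function assessed with the Six-item Cognitive Impairment Test, and the Dutch short form Informant Questionnaire on Cognitive Decline in the Elderly".
- Secondary outcome measures gives the time points but names no instrument: "cognitive and physical function at baseline, three, and six months post-discharge".
- Data collection assigns a role to each instrument. For the patient: "The Six Item Cognitive Impairment Test (6-CIT) is used to evaluate participants’ cognitive function". For the caregiver: "Primary caregivers are asked to complete the IQCODE-N in order to reflect on the participant’s cognitive function prior to hospitalisation". This is the only place that describes how the IQCODE-N is collected.
- Follow-up assessments states what is done at three and six months: "patients are contacted by telephone by one of the observers to perform the Katz ADL, the Lawton IADL scale, and the 6-CIT". The IQCODE-N is not on this list.
- Statistics sends secondary efficacy measures that are not normally distributed to the Mann–Whitney test and normally distributed continuous data to Student's t test. It describes no adjustment for a baseline value.

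**The concern.** An outcome in a randomised comparison has to be something that the treatment could change. The abstract presents two instruments for the cognitive outcome, but the collection schedule makes one of them a description of the patient before admission.

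Two things are at stake. First, a between-arm test of the IQCODE-N could be reported as an efficacy result when it can only reflect how the randomisation fell. Second, readers of the abstract would expect an informant-based measure of cognitive change beside the patient test, and the schedule provides none. The Background names long-term cognitive decline as a consequence of delirium, and the Discussion promises evidence on outcomes after discharge. It should therefore be clear which measure carries the cognitive comparison.

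**Working it through.** There is no stated figure on this point to reproduce. The article's one design calculation, for the primary outcome, was checked as background. For 20% v 10%, two-sided 5% and 80% power, the pooled-variance formula gives

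n = [1.96·√(2·0.15·0.85) + 0.842·√(0.20·0.80 + 0.10·0.90)]² / 0.10² ≈ 199 per arm.

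The article states 195, at which power is 79.2%. That is close enough, and the present point does not depend on it.

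The check is a comparison of sections.

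| Section | 6-CIT | IQCODE-N |
|---|---|---|
| Abstract, Methods/Design | instrument for the cognitive outcome | instrument for the cognitive outcome |
| Secondary outcome measures | not named (baseline, 3 and 6 months) | not named (baseline, 3 and 6 months) |
| Data collection | patient's cognitive function | caregiver's account of pre-hospital function |
| Follow-up assessments | listed at 3 and 6 months | not listed |
| Discussion | face to face on admission, telephone later | not mentioned |

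1. Count of measurements: the IQCODE-N has one described collection, about the pre-admission state, and none at the two follow-up contacts. The 6-CIT is the only cognitive instrument at both.
2. Let X be cognitive function before hospitalisation and A the allocated arm. X is fixed before A is drawn and A is random, so X is independent of A. The expected difference in X between haloperidol and placebo is zero whatever the drug does.
3. A two-sided 5% test of the IQCODE-N between arms would therefore be significant about 5% of the time by chance alone. A significant result would not indicate benefit or harm, and a non-significant one would not indicate lack of effect.
4. X can still be useful as a covariate. If pre-admission cognition predicts the follow-up 6-CIT, adjusting for it removes chance imbalance and some residual variance. The article gives no correlation, so the gain in precision cannot be quantified here.

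**The case against.** The strongest reply is that this is loose wording in an abstract. The body's outcome list includes baseline in the cognitive outcome, and the IQCODE-N is a baseline instrument. The abstract does not say that it is repeated or compared between arms, and Statistics does not name it as an endpoint. Much of this stands, and it is why the point is modest. It does not remove the contradiction: a pre-admission rating is not an outcome, and the abstract is where the instruments are tied to the outcome.

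A second reply is that the article condenses a full protocol, which may schedule a follow-up IQCODE-N. That is possible. But the article does state the reference period and does list the follow-up instruments, so the point rests on what it says. Whichever version is right, one of these sections needs correcting.

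A reader might also infer three stronger points, which the article does not support.

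- *That the telephone 6-CIT is an overlooked weakness.* The Discussion discloses it ("Although the 6-CIT has not been validated for telephone administration, we considered it to be accurate for use over the telephone") and gives a rationale by analogy with another telephone screener.
- *That the patient is the only informant at follow-up.* The same calls are to obtain all-cause mortality, which a deceased patient cannot report, so the wording is not a complete list of sources. Rules for proxy respondents are detail that an article may leave to the full protocol. The Discussion also cites support for the Katz by telephone.
- *That patients who decline will miss the call, and that any difference between arms must then shrink.* The article gives no completion rates and defines no threshold for decline. Nor does the general statement hold. As an illustration with every rate assumed, take true decline d of 30% v 20%, 5% of non-decliners missing, and a fraction m of decliners missing equally in both arms. Observed decline is d(1−m)/[d(1−m) + 0.95(1−d)].

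| m | Observed decline | Difference (points) | Risk ratio | Odds ratio |
|---|---|---|---|---|
| no missing data | 30.0% v 20.0% | 10.0 | 1.50 | 1.71 |
| 25% | 25.3% v 16.5% | 8.8 | 1.53 | 1.71 |
| 50% | 18.4% v 11.6% | 6.8 | 1.58 | 1.71 |
| 70% | 11.9% v 7.3% | 4.6 | 1.63 | 1.71 |

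The absolute difference falls, the risk ratio rises, and the odds ratio stays at (0.30/0.70)/(0.20/0.80) = 1.71. A claim of general attenuation therefore fails even on assumptions chosen to favour it.

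**Conclusion.** The contradiction between the abstract, Data collection and Follow-up assessments is real. As scheduled, the IQCODE-N is a pre-randomisation characteristic that cannot show a treatment effect, and the 6-CIT is the only cognitive measure taken after randomisation. One of the two instruments named for the cognitive outcome thus contributes nothing to the randomised comparison.

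The consequence is limited to how one secondary outcome is defined and analysed. The primary outcome, the sample size and the primary chi-squared test are untouched, and no numerical bias is shown.

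The conclusion rests on two assumptions: that the article's follow-up list is complete as regards cognitive instruments, and that the caregiver form reflects the pre-admission state as described. The article does not say on which day the form is completed. A form filled in after treatment has started could be coloured by the hospital course, and would then be less suitable as a covariate, but it would still not measure cognition at follow-up.

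**What to change.** Reconcile the abstract, Secondary outcome measures, Data collection and Follow-up assessments:

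1. Remove the IQCODE-N from the secondary outcomes and describe it as a baseline characteristic.
2. Name the 6-CIT at three and six months as the cognitive outcome.
3. In Statistics, compare the follow-up 6-CIT between arms with a regression model that includes treatment, baseline 6-CIT and baseline IQCODE-N, rather than by the unadjusted test alone. Use the IQCODE-N as a covariate only where the form was completed before study treatment could influence the answers, and say how missing forms are handled.
4. If a follow-up IQCODE-N is in fact planned, list it under Follow-up assessments with its timing and the period that the caregiver is asked to judge.

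Steps 1, 2 and 4 cost only wording. Step 3 adds a little analysis work and uses data already collected. Its drawback is that some caregiver forms may be missing, so the covariate will be incomplete. Adding a new follow-up IQCODE-N is not needed to resolve this point. It would bring its own question of reference period, which the article does not address.

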**Discussion:**

The HARPOON study will provide relevant information on the efficacy and safety of prophylactic haloperidol treatment for in-hospital delirium and its effects on relevant clinical outcomes in elderly at-risk medical and surgical patients.

**Trial registration:**

EudraCT Number: 201100476215; ClinicalTrials.gov Identifier:
NCT01530308; Dutch Clinical Trial Registry:
NTR3207

## Background

Delirium is a serious and frequently occurring complication of (acute) illness in older hospitalised patients with prevalence rates of more than 30%
[1]. Delirium is a neuropsychiatric syndrome characterised by a disturbance of consciousness which has an acute onset and fluctuating course, typically developing within hours and lasting for several days to weeks or even months
[1-3].

In older patients, development of in-hospital delirium is associated with a range of negative patient outcomes such as increased hospital length-of-stay, long-term cognitive- and functional decline, new institutionalisation, and increased mortality
[4-6], thereby also leading to substantial healthcare costs
[7]. Because of the associated healthcare and economic burden, multicomponent non-pharmacological intervention strategies targeting delirium risk factors in the hospital setting have been introduced. Although they are effective in reducing delirium incidence in elderly general medicine and surgical patients
[8,9], their effectiveness seems largely to depend on protocol adherence
[10] which may be low due to high staff workload. In addition, non-pharmacological multicomponent hospital-based interventions do not seem to affect post-discharge outcomes such as cognitive or functional status, and nursing home placement
[11]. Low-dose haloperidol prophylaxis has been shown to lower delirium incidence in older postoperative intensive care unit (ICU) patients
[12,13], and duration and severity in (mainly elective) hip-surgery patients
[14]. However, the effect of haloperidol prophylaxis on in-hospital delirium development and post-discharge outcomes in an older general medicine and surgical patient population has not been studied yet.

This paper describes the design of the multicenter, randomised, double-blind, placebo-controlled clinical trial to evaluate the efficacy and safety of early prophylactic treatment with low dose haloperidol on in-hospital delirium, and post-discharge outcomes in acutely admitted older medical and surgical patients.

## Methods/Design

### Research objectives

#### Primary research objective

To study the differences in in-hospital seven-day delirium incidence after acute admission for both general medicine and surgical specialties in older at-risk patients treated early with prophylactic haloperidol or placebo.

#### Secondary outcome measures

Severity and duration of delirium; number of delirium-free days; hospital length-of-stay; adverse events; all-cause mortality in-hospital and within six months post-discharge; cognitive and physical function at baseline, three, and six months post-discharge; new institutionalisation post-discharge; number of hospital admissions within six months post-discharge.

### Study design

The HARPOON study is a multicenter, investigator initiated, stratified randomised, double-blind, placebo-controlled clinical trial with a six-month follow-up period. The study design is demonstrated in Figure 
1. All at-risk patients aged 70 years or over presenting to the emergency department (ED), admitted for general medicine or surgical specialties will be screened for predefined in- and exclusion criteria as described in the section ‘Study population and recruitment’. Increased risk for developing delirium during hospital admission will be assessed according to specific delirium risk questions (Figure 
2) based on the Dutch Hospital Patient Safety Program (in Dutch: VMS Veiligheidsprogramma
[15]). This program was developed to systematically improve patient safety on 10 priority themes, which is now standardised hospital care in all Dutch hospitals since 2013. One of these themes is ‘Vulnerable elderly’
[15], which aims to reduce avoidable loss of function caused by complications of hospitalization and includes detection (risk assessment), and implementation of prevention and intervention measures for:

**Figure 1 F1:**
[figure not shown]
Design of the HARPOON study.

**Figure 2 F2:**
[figure not shown]
**VMS delirium risk questions.** Each positive answer values 1 point, a total score of 1 point or higher indicates the patient is at-risk for in-hospital delirium.

1. Malnutrition, including stimulation and measurement of nutritional intake by nutrition assistants, and dietary consultation;

2. Falls and mobility impairments, including adequate footwear, stimulation of physical activity in or out of bed, and if needed, (daily) occupational and physical therapy; and

3. Delirium.

With respect to delirium, the VMS program based standardised hospital care covers identification and modulation of precipitating delirium risk factors such as medication reviews and orientation and noise-reduction measures, creating an optimal background regimen for conduction of this trial in all participating hospitals. Patients who positively confirm one or more of the VMS delirium risk questions (VMS ≥1) are considered at-risk for developing delirium during hospital admission. Patients with VMS 0 on first evaluation are not eligible for this study. Eligible patients will be asked for informed consent. In case of inability to write, patients must provide verbal consent in the presence of an independent witness (preferably patients’ proxy) who may then sign the informed consent form. The study medication, haloperidol 1 mg or identical placebo tablets, will be given orally to participants twice daily at 12 pm and 8 pm for a maximum of seven consecutive days (14 treatment dosages) on top of standardised care based on the implemented VMS program ‘Vulnerable elderly’. During the seven-day intervention period nursing staff will screen participants for delirium symptoms. Additionally, a trained observer (physician or geriatric nurse) will daily visit participants to detect the presence of delirium, register potential adverse events based on 24-hour nursing observations, clinical judgement, and electrocardiogram (ECG) monitoring, and to check for adherence to standardised adequate environmental manipulations for delirium such as orientation measures. For patients who have not developed delirium within seven days of initiation of the study intervention, daily assessment stops. Patients who develop delirium are evaluated daily by the observer to record delirium severity and duration until symptoms diminish. Study drug administration is terminated early if a participant develops delirium, is transferred to a non-participating care unit such as the ICU, refuses further participation in the trial, the QTc interval is more than 500 milliseconds (ms), is discharged from the hospital, or dies within seven-day of initiation of the study intervention. In case of established delirium or if the assigned study intervention is thought to have a direct influence on the patient’s treatment, the treating physician will request for unblinding and may further decide on treatment. For unblinding of treatment assignment, the treating physician is able to contact the VUmc consultant pharmacist through a central telephone number 24 hours a day, seven days a week.

This study is conducted according to the Declaration of Helsinki. This trial is approved by the accredited Medical Ethical Committee of VU University Medical Center (VUmc) Amsterdam, the Netherlands (reference number: 2012.177). The executive boards of Isala Hospital Zwolle, Spaarne Hospital Hoofddorp, Rijnland Hospital Leiderdorp, Jeroen Bosch Hospital’s Hertogenbosch, and Medical Centre Alkmaar (MCA), all located in the Netherlands, have provided local feasibility approval.

### Location and setting

This study is primarily conducted at VUmc, a 733-bed teaching hospital located in Amsterdam, the Netherlands. Secondary study locations include the Isala Hospital Zwolle (976 beds), Spaarne Hospital Hoofddorp (455 beds), Rijnland Hospital Leiderdorp (420 beds), Jeroen Bosch Hospital ’s Hertogenbosch (730 beds), and MCA Alkmaar (485 beds), the Netherlands.

### Study population and recruitment

#### Inclusion criteria

Patients aged 70 years and over are eligible when acutely admitted to the hospital through the ED for general medicine or surgical specialties, are able to speak and understand Dutch or English language, are at-risk for delirium on admission (VMS ≥1), are available for inclusion within 24 hours after admission, and are able to provide informed consent. Patients are considered competent to provide informed consent if – after having spoken with the patient – the observer and/or the treating physician agree on the ability of the patient to understand and/or recall relevant study information, including the purpose of the study, its experimental nature, potential benefits and risks, the right to withdraw, and confidentiality of collected data, and to make a voluntary decision to participate. If their cognitive competence is in question, the patient will be regarded as ineligible.

